## Abstract

**Background:**

Coercive measures are among the most controversial interventions in psychiatry. There is a large discrepancy between the sheer number of high-quality guidelines and the small number of scientifically accompanied initiatives to promote and evaluate their implementation into clinical routine. In Germany, an expert group developed guidelines to provide evidence- and consensus-based recommendations on how to deal with violence and coercion in psychiatry.

**Methods:**

The study presented examines whether coercive measures on psychiatric wards can be reduced by means of an operationalized implementation of the guidelines “Prevention of coercion: prevention and therapy of aggressive behavior in adults”. Out of a set of 12 interventions offered, wards are free to choose three interventions they want to implement. The primary outcome is the number of coercive measures per bed and month/year. Secondary outcomes are cumulative duration of coercive measures per bed and month/year. The most important control variable is the number of aggressive incidents. We plan to recruit 52 wards in Germany. Wards treating both voluntary and compulsorily admitted patients will be included. A 1:1 stratified randomized controlled trial will be conducted stratified by the amount of coercive measures and implemented aspects of the guidelines. In addition to the control group analysis, a waiting list design allows a pre-post analysis for all participating wards of the waiting list group. A parallel qualitative study will examine factors related to successful implementation and to successful reduction of coercion as well as relevant barriers.

**Discussion:**

We are planning a nationwide study on the implementation of evidence- and consensus-based guidelines in psychiatric hospitals. This study intends to promote the transfer of expert knowledge as well as results from clinical trials into clinical routine with the potential to change supply structures in mental health sector.

**Clinical Trial Registration:**

www.isrctn.com, identifier ISRCTN71467851.

## Introduction

Whether and under what circumstances the use of coercion in psychiatric treatment is justified is one of the oldest and most controversially discussed questions in psychiatry. Since psychiatric hospitals have long been assigned regulatory tasks in addition to medical ones, the discussion is caught between treatment and safety, patient rights and the rights of third parties. Today, most psychiatric and legal experts agree that coercive measures may only be used if other measures were not sufficient to avert danger from the patient or others. In 2011, 2016, and 2018, coercive measures in psychiatric care were the subject of landmark rulings by the German Federal Constitutional Court, each of which entailed significant changes to the Mental Health Laws (1–3).

The German Federal Constitutional Court has emphasized that mechanical restraint in particular should only be used as a “last resort” (2). In 2016, 6.7% of all admissions to psychiatric hospitals experienced freedom-restrictive coercive measures such as seclusion and restraint according to the data of the register in the German federal state Baden-Wuerttemberg (4). Relative to a population of approximately 11 million inhabitants, 30,386 of such measures took place (4). The subject has been classified as highly relevant by the German Association for Psychiatry, Psychotherapy and Psychosomatics (DGPPN) and is also the subject of numerous statements (5). Against this background, the Clinical Practice Guidelines “Prevention of coercion: prevention and therapy of aggressive behavior in adults” (6) was published in 2018. These are S3 guidelines, what means that they have achieved the highest methodological quality of guidelines developed in Germany and that they are evidence and consensus based taking into account all available scientific literature and the opinion of acknowledged specialists in the field. A comprehensive research of the scientific evidence as well as a structured consensus-finding process involving all relevant experts was incorporated into the recommendations. These guidelines define aggressive behavior as an interactive process. Thus, aggressive behavior in psychiatric institutions results from the interaction of individual experience and behavior on the part of patients, relatives and employees, situational characteristics and an escalation component. This means that aggressive escalations as well as coercive measures by psychiatric institutions can be modified. There is already a wealth of research on the reduction of coercion and violence (7). Measures which were effective in clinical trials were staff educational programs and regular training of the employees (8), enrichment of the ward environment, structured risk assessment and early interventions [e.g., Brøset Violence Checklist (9)], individualized treatment planning, especially advanced care planning (10) for patients who already experienced violence and coercion, as well as debriefing techniques. Interventions were especially helpful if they were combined with each other, incorporated organizational changes and were endorsed by the management of the clinic. Therefore, several complex interventions consisting of different measures were developed in the past few years, e.g., internationally Six Core Strategies (11) and Safewards (12, 13) and in Germany Weddinger Modell (14). While the Six Core Strategies (11) include top-down-elements focusing on the organization of a psychiatric ward or clinic, Safewards emphasizes the communication among patients and staff on a specific ward (12). The Weddinger Modell, developed in 2010 in Berlin, Germany, is an innovative model of psychiatric care focusing on recovery, participation, supported decision-making and the prevention of coercive measures on psychiatric wards (14).

Until recently, high-quality guidelines were mainly available for acute emergency situations, as, e.g., for aggressive agitation (15). The German clinical practice guidelines, on the other hand, also attempt to summarize the preliminary work on de-escalation and violence prevention in practical recommendations. They were developed with the substantial participation of patient and family associations and offer detailed evidence- and consensus-based recommendations for the first time on how psychiatric clinics can meet these challenges.

Dealing with violence and coercion is regarded as one of the most important aspects of the quality of psychiatric care (16). For many years, the topic has also been classified as highly relevant in Germany, especially against the background of constantly increasing demands for respect of patient autonomy on the one hand and the protection of employees’ rights by the Occupational Health and Safety Act on the other hand. In addition, patient and family associations are calling for improvements particularly in this area. People with mental health problems and their relatives perceive seclusion and restraint as anti-therapeutic. In a qualitative study, measures restricting freedom were regarded as human rights violations even if they were recognized by affected patients as necessary to avert risks (17). The Federal Constitutional Court has clarified that there is a considerable need for action with regards to reducing the use of restraints. The named guidelines show how this can be achieved, taking into account the available evidence. In 2018, the Gemeinsamer Bundesausschuss (Federal Joint Committee, a committee that determines what is paid for by the statutory health insurance fund) even addressed this issue in relation to the structure of the remuneration system in the German health system.

Worldwide, it is found to be highly problematic that there is considerable variability in the frequency of application of coercive measures between hospitals (18, 19), which could also be confirmed for Germany (20, 21). Therefore, beginning in the years after 2000, a common system of data registration and hospital comparisons had been introduced. This was accompanied by continuous efforts of a quality circle, showing that this variance can be reduced (22). This also suggests that implementation of measures to reduce coercion could have the potential to reduce coercive measures and the variance between clinics. In this line, we used the guidelines published in 2018 to derive operationalized recommendations for a) care regions, b) psychiatric hospitals, and c) psychiatric wards. We deemed it important to provide only recommendations that are measurable in terms of the degree of implementation. The recommendations for implementation were adopted in November 2018 by the German Association for Psychiatry, Psychotherapy and Psychosomatics (DGPPN).

The recommendations can be implemented as a complex intervention. Thus, they arrive directly at the level of the psychiatric ward, measurable with implementation indicators and at the level of patient care in terms of impact on coercive measures and assaults. A sustainable goal of the project is expected to be the improvement of care processes in one of the most sensitive areas of psychiatric treatment.

Due to their very heterogeneous size and structure, entire hospitals are difficult to address and to evaluate. This applies even more for the care regions, since a large number of other actors such as police, courts, and service providers are involved. As with most international evaluations of such interventions, the most appropriate target level is the ward level. To date, there is a remarkable disparity between the high number of evidence-based guidelines and the comparatively low number of concrete implementation recommendations and the even lower number of implementation studies and evaluations. While the implementation of peri-operative interventions, for example, seems comparatively easy to operationalize and measure, the challenges regarding the diverse and complex recommendations in psychiatric care are obviously greater. A review in 2017 identified only 17 studies comparing guideline implementation strategies versus routine care and found no consistent effects on provider performance (23). Some positive results can be mentioned: In the Netherlands, it was recently demonstrated that guidelines on suicide prevention could be successfully implemented in 24 institutions. However, there was no evidence at the level of patient-related outcomes (24). In Canada, an implementation strategy for schizophrenia guidelines was developed and successfully implemented at a single hospital (25). The high costs involved in developing high-quality guidelines and the low benefits of not applying them have been the subject of repeated criticism. Concerns have even been voiced by guideline authors themselves in recent years (26).

The aim of this study is to accomplish the final and most difficult step of guideline implementation: The first step was the development of guidelines together with many experts and all relevant organizations of professionals, patients, and relatives. The second step was the development of the 12 concrete recommendations for implementation and instruments to measure the effects at the level of psychiatric wards. There is good evidence for all 12 individual elements and a high consensus among 23 expert groups, including professionals, patients, and their relatives who were involved in the development of the guidelines. The third step was a pilot study in five psychiatric hospitals ending in December 2019, testing the feasibility of the procedure and the interventions (27). The wards were accompanied for six months by psychiatrists and nursing consultants from the study team. It was agreed in advance that three of the twelve recommendations would be newly implemented. Wards were only included in the pilot study if the nursing and medical directors agreed to support the implementation. At the beginning of the six months implementation period, a one-day awareness workshop with the medical and nursing ward management, the team members, and the next higher level of medical and nursing hierarchy was held. Consultants and ward staff commonly evaluated (i) which recommendations were already realized in the ward and to which extent and (ii) which recommendations should be introduced as part of the pilot study. Given the urgency of the topic, it can be assumed that so far there is no psychiatric hospital which has until now not implemented any interventions or strategies to reduce coercion. At the same time, no clinic has fully implemented all recommendations suggested in the guidelines. The consultants and the teams agreed upon a timetable with milestones. Two half-day intermediate workshops for monitoring and further counseling were scheduled. In the meantime, the wards always had the opportunity to contact their consultants by telephone or e-mail.

The fourth step will be a randomized controlled study with sufficient statistical power to test the effectiveness of the intervention on a ward-basis. For this step the design and methods will be described in this study protocol.

## Methods

### Study Design

This multicentre study applies a mixed-methods design. In this interventional trial, wards are randomized in a 1:1 ratio to either an intervention or a control condition (waiting list), stratified by the amount of coercive measures per bed and month/year and the implemented aspects of the guidelines to matched pairs. In addition, a waiting-list control design allows for a pre-post analysis for participating wards of the waiting list group. Furthermore, this design allows for analyzing if observer effects already lead to a reduction of coercive measures between the baseline and the start of the intervention as well as for assessing potential spill-over effects in the control group during the waiting time. After 12 months, control wards will receive the intervention. Pre-post analysis will also be done or interventions wards which provide additional data of one year of follow-up after the intervention. Moreover, a complementary qualitative trial in form of interviews with participating staff will be performed.

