### Standard of Care on Control Wards

The legal requirements (mental health laws, civil code) already require the use of coercion to be limited to a necessary minimum. The participating wards should continue to apply their current strategies to prevent coercion and violence, even if they are randomized into the control group and even if these strategies are also mentioned in the 12 interventions. New structured programs especially with external supervision to reduce coercion and violence further should not be implemented in this phase. However, control wards will be informed about the program and its possibilities and spill-over effects cannot be ruled out. To detect such effects, a second measurement of implementation status and outcomes will take place on the control wards before the beginning of the intervention after the waiting list status.

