### Instruments

At the beginning of the trial, a joint evaluation by study staff and the ward team will be carried out for each of the 12 recommendations on a scale from 0 (= not implemented at all) to 9 (= fully implemented). This weighting is realized by with a Likert scale with typical anchor examples for each recommendation for the scores 0, 3, 6, and 9.

For the recording of violent incidents, the guidelines recommend the use of the SOAS-R (28). This instrument is most widespread throughout Europe and has already been introduced at many clinics in Germany. It is a well validated instrument with a score ranging from 0 to 22 (higher ratings stand for more severe incidents). In order to compensate problems of under- and over-reporting as much as possible, events will be considered only above a minimum score of 10 points. This allows both individual events and their severity to be taken into account. Furthermore, SOAS-R outcomes can be treated as continuous variables also. However, some of the participating hospitals will have introduced other, possibly less standardized instruments in their clinical practice. To avoid unwanted effects of increasing awareness in the course of the introduction of a new instrument, these hospitals will be advised to continue with their introduced instrument without any change in the practice of application.

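### The waiting-list arm cannot show whether observer effects reduce coercion, because its change over time also contains secular trend and spill-over

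*Protocol article*

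**What the plan says.** The section Study Design attributes two diagnostic properties to the waiting list. First, "this design allows for analyzing if observer effects already lead to a reduction of coercive measures between the baseline and the start of the intervention". Second, it is useful "as well as for assessing potential spill-over effects in the control group during the waiting time". The window is fixed: "After 12 months, control wards will receive the intervention".

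The section Standard of Care on Control Wards concedes that "control wards will be informed about the program and its possibilities and spill-over effects cannot be ruled out". It then gives the means of checking this: "To detect such effects, a second measurement of implementation status and outcomes will take place on the control wards before the beginning of the intervention". Two things are thus re-measured on control wards: coercion, and the implementation status defined under Instruments (12 recommendations, each scored 0 to 9, rated jointly by study staff and ward team).

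Under Interventions, the first workshop supplies the data for matching and randomisation, so every ward in either arm has it. Under Outcomes, a secondary endpoint is the change from waiting period to intervention period within the waiting-list group. Under Statistical Analysis, the primary test compares ward pairs between arms.

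**The concern.** An observer effect can be estimated only against something unobserved, and spill-over only against something uninformed. The design as described has neither. A fall in coercion on control wards during the wait could come from being observed, from hearing about the programme, or from a movement that would have occurred anyway. Study Design nevertheless presents the waiting list as able to analyse the first of these, and Standard of Care on Control Wards offers the second measurement as the detector of spill-over.

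What is at stake is the reading of the control arm, not the primary test. If control wards improve, the text invites an attribution that the coercion data cannot support. The secondary before-after endpoint is exposed to trend in the same way.

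**Working it through.** **Inputs.** 26 pairs, hence 26 control wards; two-sided 5% level; standardised effect 0.6 (Sample Size). Waiting period 12 months (Study Design). No trend is given, so its size below is an assumption, shown over a range.

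**The plan's own figure.** Power of a paired t-test is P(|T| > t(0.975, n−1)), where T is noncentral t with n−1 degrees of freedom and noncentrality d√n. At d = 0.6, n = 23 gives 0.785 and n = 24 gives 0.804, so the stated 24 pairs reproduces. Adding 5% to 10% for the Wilcoxon test gives 24 × 1.05 = 25.2 to 24 × 1.10 = 26.4, consistent with 26 pairs. Nothing below changes the sample size.

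**Step 1: what the means can identify.** Write b for baseline, t for trend over the wait, o for the observer effect, s for spill-over on control wards and e for the treatment effect. Effects are taken as additive, observation as equal in both arms, and baseline as preceding observation, which gives the claim its best chance.

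| Arm | Baseline | End of waiting period |
|---|---|---|
| Control | b | b + t + o + s |
| Intervention | b | b + t + o + e |

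- Control arm alone: the change is t + o + s. Two means carry four unknowns (rank 2), so only the sum of the last three is estimable.
- Both arms: rank 3 for five unknowns. The difference in change is (t + o + e) − (t + o + s) = e − s. Trend and observation always appear together as t + o, so the second arm does not separate them.

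**Step 2: what a before-after test would report.** Set o = s = 0 and let only a trend act, in units of the standard deviation of the ward-level change. With n = 26 the noncentrality is the trend × √26 = trend × 5.10.

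| Assumed trend (SD) | Paired t-test significant | Paired Wilcoxon significant (4,000 simulated trials, normal changes) |
|---|---|---|
| 0 | 5% | 5% |
| 0.2 | 16.5% | 16% |
| 0.4 | 50% | 49% |
| 0.6 | 84% | 82% |

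Every significant result in the last three rows would be a wrong attribution if it were read as an observer effect or spill-over.

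**Step 3: what the implementation scores add.** A rise in scores on control wards shows uptake of guideline elements during the wait, which bears on spill-over. It gives no reading of o, because it does not measure the effect of being observed on the count. It also does not show that a fall in coercion was caused by the uptake, or that the uptake came from the trial: the Introduction reports that the recommendations were adopted by the national professional association in November 2018. The rating is joint, and Statistical Analysis says raters are not blinded.

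**Step 4: the secondary before-after endpoint.** With t₁ and t₂ the trend reached in the waiting and intervention periods, and e′ the effect once control wards are treated, the change is (b + t₂ + o + e′) − (b + t₁ + o + s) = (t₂ − t₁) + (e′ − s). The trend term stays. By then the other arm has already been treated, so no untreated concurrent group is left to remove it.

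**The case against.** The strongest reply is that the trial does not depend on this change. The primary test is a concurrent randomised comparison within pairs. Trend and observation common to both arms cancel, as Step 1 shows, and spill-over can only shrink the contrast. No test, threshold or decision rule is attached to the control-arm change. All of this stands and limits the weight of the point.

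Four stronger readings are tempting, and the documents do not support them.

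- A reader might infer that the contamination safeguard is worthless. It is not: implementation status is re-measured as well as coercion, and 12 anchored items can show uptake on control wards.
- A reader might infer that it is the only protection of the comparator. Under Randomization, matched wards must not belong to the same hospital, and Standard of Care on Control Wards adds: "New structured programs especially with external supervision to reduce coercion and violence further should not be implemented in this phase".
- A reader might infer that the article itself documents a falling trend. The Introduction says of the common data registration and hospital comparisons: "This was accompanied by continuous efforts of a quality circle, showing that this variance can be reduced". That concerns variance between hospitals, not the mean. The court rulings it cites date from 2011, 2016 and 2018, before the ethics approval of September 2019. A continuing trend is plausible but not shown.
- A reader might infer that a null result would be explained away as leakage. Nothing in the article says so.

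It can also be said that the wording is mild, that the spill-over phrase promises only assessment, and that a condensed article leaves modelling to fuller documents. This stands for spill-over. It does not rescue the statement on observer effects: that is a claim about what the design permits, and no model recovers a quantity that the described data do not identify.

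**Conclusion.** The point holds in a limited form. On the coercion outcome, the control-arm change from baseline to the end of waiting estimates the combined effect of trend, observation and spill-over. The Study Design statement on observer effects therefore claims a property that the described design lacks. The second measurement can show uptake of guideline elements but cannot attribute a fall in coercion to spill-over. The primary comparison is not biased by common trend or observation and is at most diluted by spill-over. The secondary waiting-period versus intervention-period change is confounded with trend.

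The size cannot be fixed from the article. Over an assumed trend of 0.2 to 0.6 standard deviations, a before-after t-test would suggest a non-existent observer or spill-over effect in 16.5% to 84% of trials. The identification result rests on additive effects and on equal observation in both arms. Any extra observation of intervention wards would be absorbed into the treatment effect and would not help to isolate o.

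**What to change.** 1. Reword Study Design and Standard of Care on Control Wards so that the waiting-period change in coercion is reported as the combined effect of trend, observation and spill-over. Attach the same trend caveat to the secondary waiting-period versus intervention-period change. Cost: wording only.
2. Name the change in item-level implementation scores on control wards as the spill-over indicator, and do not call a fall in coercion spill-over without it. Cost: none in data, since the scores are already planned.
3. Where wards' routine records allow, collect aggregated counts for a period before the first workshop and look for a break from that trend. Treat a break as suggestive, not conclusive, evidence of an observer effect, because observation and information about the programme may begin together. Cost: additional entries in the tables that hospitals already fill in.

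The downside of the third step is uneven data. Data Collection describes legally standardised recording only for Baden-Württemberg, so pre-enrolment records elsewhere may be shorter or less uniform. A uniform long series for all wards, or a register comparison with non-participating hospitals, is not shown to be available and should not be relied on.
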